### Study infrastructure

To reach sufficient participants and maximise their ability to participate, the OC proposed collaborating with a selection of clinicians treating women with ovarian cancer either known to the Coalition, or through the extensive network of IGCS members. An initial target list of 31 LMICs was drawn up and approaches made to clinicians and national and regional gynecologic oncology societies. In total, 113 clinical sites have been recruited using snowballing methods across 24 countries (Fig 1). Classification of country income level was determined using the World Bank open data, accessed in June 2021 [29].

**Fig 1 pone.0298154.g001:**
[figure not shown]
Participating countries by income-level World Bank status June 2021.

Within each country, a lead clinician (CLC) was assigned to coordinate the national activity and secure approvals by local or national ethics committees as required. As an example, the protocol submitted in Kenya, is included as a S2 File. CLCs advised on the languages needed and provided contacts for translators who could meet the requirements of the various ethics committees. The survey has been translated into 28 languages using the agencies recommended by the CLCs, and translations checked by back translation where required by national ethics, the clinical team, the study team, and by one or two local patients. The CLC is responsible for the implementation of the protocol, choosing optimal methods of sample selection and data collection for their setting. The CLC is responsible for building their network of participating sites, each with a local site lead (LSL). Depending on the health infrastructure and resources available, countries may have between one and 12 sites, ideally representing the typical range of care women might receive within the country. This is summarised in Fig 2.

**Fig 2 pone.0298154.g002:**
[figure not shown]
Governance structure of the study.

As part of the study, each CLC also participates in a qualitative study using semi-structured interviews to explore the care of women with ovarian cancer in their country and the opportunities for progress. They also provide additional information about care in their country collected in survey format (S3 and S4 Files). These elements will be analysed separately and used to help provide context for the global analysis of the Every Woman Study™ LMIC Edition, and content for the country reports.

Each LSL is responsible for identifying research assistants for the study (nurse, researcher, doctor, social worker or similar with experience in speaking with patients with ovarian cancer), to administer the questionnaire and enter data onto the REDCap electronic data capture tools hosted at the International Gynecologic Cancer Society [30, 31]. REDCap (Research Electronic Data Capture) is a secure, web-based software platform designed to support data capture for research studies, providing 1) an intuitive interface for validated data capture; 2) audit trails for tracking data manipulation and export procedures; 3) automated export procedures for seamless data downloads to common statistical packages; and 4) procedures for data integration and interoperability with external sources.

The research assistants are known as an administrator of the study. To keep consistency in terms of data collection, the administrators are kept to a minimum number per site, ideally one or two. It is important for local teams to consider which person or role will be able to communicate most effectively with the women, bearing in mind their situation and who they would feel most comfortable talking to. This can vary between countries and was highlighted during the testing phase. Each CLC, LSL and administrator is provided with access to REDCap. Training on the system is provided by the Project Management team (live sessions, video recordings and/or PowerPoint guides).

### Sample selection

Initially the OC recommended a standardised single approach to sample selection, with all patients diagnosed within the last five years at a participating site being approached for inclusion in the study. This would have allowed for inclusion of survivors with a wide-spread time since diagnosis, and reached patients who might otherwise have stopped treatment or be in remission. However, given the diversity of resources, attendance patterns, and access to patient records between countries and even participating centres within a country, the OC decided a single approach was not feasible. A randomised approach was also not deemed suitable given the challenges ensuring consistency in implementation across many sites. Instead, a convenience sampling approach was approved, offering three different models listed below. To compensate for the variety of approaches, the method of sample selection will be recorded for each patient to allow for data stratification if required. CLCs suggest all participating centres in their country follow the same approach, but this is not mandated. The sample selection approaches, and associated caveats are as follows:

The site team reviews all cases on their records that have been seen in the previous five years, with a view to contacting eligible ovarian cancer patients and inviting them to participate. This approach is dependent on availability of staff resource, accessible patient records and reliable communication methods with patients. It might also catch patients who have previously stopped treatment but may also require them to attend a new appointment if they cannot be reached by email, or WhatsApp, and so completion rates may be lower;The site team reviews all cases of ovarian cancer patients who have recently attended an appointment, working backwards in a sequential manner, until they meet the minimum or preferred sample size. This requires extra resource and good record-keeping, and may mean the sample selected is skewed to those with a more recent diagnosis; andThe site team reviews all cases of ovarian cancer patients due to attend a forthcoming appointment in person or virtually, inviting eligible patients to participate at that appointment. This approach requires less staff resources, as patient notes and attendance in clinic is already factored in. It may also improve completion rates. However, this approach may result in the inclusion of a greater proportion of patients with a more recent diagnosis, those on active treatment or experiencing complications, and can add time to clinic appointments.

### Sample size

The minimum sample size for each country is based on GLOBOCAN estimates of five-year disease prevalence in the country, producing results at the 95% confidence level (+/- 10%) [2]. CLCs can choose to recruit more patients to improve confidence intervals in their standalone results. In total, the study aims to collect data from at least 1534 women, which would provide results at a 95% confidence level, +/- 2.5%, based on global five-year prevalence. Should each of the 24 countries (3 low, 11 lower-middle and 10 upper-middle income countries) collect their minimum data, the sample size would be 2,160 (Table 2).

**Table 2 pone.0298154.t002:** Expected sample sizes by country and income level.

REGIONAL AREA	COUNTRY	WORLD BANK INCOME STATUS (JUNE 2021) [29]	MINIMUM SAMPLE SIZE	PREFERRED SAMPLE SIZE	FIVE-YEAR PREVALENCE OF OVARIAN CANCER
**Sub-Saharan Africa**	Ghana	Lower-middle	92	327	2190
	Kenya	Lower-middle	92	330	2314
	Malawi	Low	79	203	431
	Mozambique	Low	70	155	259
	Nigeria	Lower-middle	95	361	6079
	South Africa	Lower-middle	94	347	3559
	Uganda	Low	89	297	1242
	Zambia	Lower-middle	78	197	403
**North Africa**	Egypt	Lower-middle	95	364	6854
	Morocco	Lower-middle	93	340	395
**South-East Asia**	Malaysia	Upper-middle	94	357	4989
	Vietnam	Lower-middle	95	346	3468
**Western Asia**	Kazakhstan	Lower-middle	93	343	3207
	Uzbekistan	Lower-middle	92	322	1997
**Caribbean, Central, South America**	Argentina	Upper-middle	95	362	6192
	Brazil	Upper-middle	96	377	18912
	Colombia	Upper-middle	95	362	6344
	Guatemala	Upper-middle	83	236	604
	Jamaica	Upper-middle	72	165	290
	Mexico	Upper-middle	95	374	13529
	Peru	Upper-middle	93	345	3398
**South-central Asia**	Bangladesh	Lower-middle	95	364	7044
	India	Lower-middle	96	383	103716
	Nepal	Lower-middle	89	297	1297
Total		Lower-middle	2160	6815	198,713

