## Introduction

### Global incidence and mortality

Ovarian cancer is the eighth most common cancer and eighth most common cause of cancer death in women worldwide [1]. GLOBOCAN estimates that in 2020 there were approximately 314,000 cases diagnosed, 207,000 deaths, and more than 823,000 women living within five years of their diagnosis. Women in low- and middle-income countries (LMICs) account for 70% of ovarian cancer cases [2]. A 42% increase in ovarian cancer incidence, and a 52% increase in mortality, has been predicted by 2040, with the greatest increase expected in LMICs driven by projected population increases [3, 4]. For example, Zambia is predicted to have an increase of 122% in ovarian cancer incidence and 132% in mortality. Further increases are expected linked to the changing prevalence of cancer risk factors, such as lack of physical activity, changing diets, additional body weight, and increasing urbanisation [5–8].

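### The ±2.5% global and ±10% country margins are simple-random-sample figures that this near-equal-per-country, site-clustered convenience sample does not deliver as stated

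*Protocol article*

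**What the plan says.** The Sample size section makes two precision statements. For each country, GLOBOCAN five-year prevalence is used to set a minimum "producing results at the 95% confidence level (+/- 10" percent). For the whole study the target is "at least 1534 women, which would provide results at a 95% confidence level, +/- 2.5%, based on global five-year prevalence". If all 24 countries reach their minimum, the total is 2,160 (Table 2). The Introduction gives the worldwide figure as "more than 823,000 women living within five years of their diagnosis".

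The design is described elsewhere. Under Sample selection, random selection is judged unsuitable and "a convenience sampling approach was approved, offering three different models listed below". Under Study infrastructure, 113 sites were recruited by snowballing, and "countries may have between one and 12 sites". Table 2 sets minimums between 70 and 96 per country, while five-year prevalence runs from 259 (Mozambique) to 103,716 (India).

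The Discussion concedes that the varied selection methods may bias results, plans sensitivity analyses by selection method, and accepts that standalone country intervals will be wide. It does not qualify either stated margin.

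**The concern.** A margin of error belongs to an estimator under a sampling design. The two margins here are computed as if women were drawn at random, from the world for the global figure and from the national prevalent population for each country. The study does neither. It takes almost the same number of women from countries whose prevalence differs by a factor of 400 (103,716/259), it recruits them in clusters at hospitals, and it selects them by convenience. The global figure is also tied to a worldwide population although the study is confined to low- and middle-income countries.

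Precision is the only sample-size justification given, and the Aim section intends the results for governments and policy makers. A reader would take ±2.5% as the accuracy of a statement about women with ovarian cancer across these countries. The article does not say what the global estimate describes (women in proportion to prevalence, countries equally, or whoever was recruited), and the margin depends strongly on that choice.

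**Working it through.** **Inputs.** From the documents: 1,534 and ±2.5%, ±10% per country, and the minimum sizes and prevalences of Table 2 (totals 2,160 and 198,713), all in Sample size; about 823,000 women worldwide (Introduction); 113 sites (Study infrastructure). Assumed: p = 0.5, which the article does not state but its figures imply, and a site ICC of 0.01 to 0.10, because the documents give none.

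**1. Reproducing the plan's figures.** n0 = 1.96² × 0.25 / e² and n = n0 / (1 + (n0 − 1)/N).
- Global, e = 0.025: n0 = 1,536.6. With N = 823,000, n = 1,533.7, which rounds to the stated 1,534. With N = 198,713 (the 24 countries), n = 1,525. The stated figure therefore uses the worldwide total.
- Country, e = 0.10: n0 = 96.0. N = 259 gives 70.3 (Mozambique, stated 70) and N = 103,716 gives 95.9 (India, stated 96). The formula matches 23 of the 24 minimums within 2 women. Morocco is the exception: its printed prevalence of 395 gives 77.4 against a stated 93.

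The arithmetic is right for a simple random sample.

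**2. Global estimate weighted by prevalence.** India: 103,716/198,713 = 52.2% of prevalence, 96/2,160 = 4.4% of the sample. With W_h = country prevalence/198,713, the variance is Σ W_h² × 0.25/n_h.
- At 2,160: variance 0.000765, half-width 1.96 × √0.000765 = 5.4 points, effective n = 0.25/0.000765 ≈ 327, design effect 2,160/327 ≈ 6.6.
- India alone contributes 0.522² × 0.25/96 = 0.000709, or 93% of that variance.
- At 1,534 spread in the same proportions: effective n ≈ 232, half-width 6.4 points.
- If Morocco's prevalence were about 2,950, the value its sample sizes imply, the 2,160 figure would still be 5.4.

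**3. Global estimate, unweighted or equal weight per country.** Unweighted: 1.96 × √(0.25/n) gives ±2.1 at 2,160 and ±2.5 at 1,534. An equal-weight average, with variance (1/24²) Σ 0.25/n_h, gives the same to one decimal.

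**4. Site clustering of the unweighted estimate.** Design effect = 1 + (m − 1) × ICC, with m = n/113, that is 13.6 women per site at 1,534 and 19.1 at 2,160.

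| Site ICC (assumed) | n = 1,534 | n = 2,160 |
|---|---|---|
| 0.01 | ±2.7 | ±2.3 |
| 0.05 | ±3.2 | ±2.9 |
| 0.10 | ±3.8 | ±3.5 |

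At 1,534 there is no slack, so any positive ICC takes the margin past 2.5. At 2,160 the margin stays within 2.5 if (2,160/1,536.6 − 1)/(19.1 − 1) ≈ 0.022 is not exceeded.

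**5. Country margins.** Without the finite-population correction, 1.96 × √(0.25/n) gives ±11.7 (n = 70), 11.5 (72), 11.1 (78), 11.0 (79), 10.8 (83) and 10.4 (89), falling to 10.0 (96). At n = 90 (±10.3 before clustering) with 19.1 women per site, the design effects are 1.18, 1.91 and 2.81 for ICC 0.01, 0.05 and 0.10, giving ±11.2, ±14.3 and ±17.3.

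**The case against.** The strongest reply is that ±5.4 belongs to an estimand the article never announces. No section promises prevalence weighting. The mention of global prevalence may only identify the population size in the formula, and the country reports are to be compared with an average over all participants (Data analysis). The Aim is to show that factors vary by country, for which near-equal allocation is sensible. This stands in part: for an equal-weight or unweighted average, 2,160 women give ±2.1 before clustering, so the 2.5% is not far off for that target. But the article does not name that target, attaches the margin to 1,534, where nothing is left for clustering, and ties it to worldwide prevalence.

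Several components are small, and this also stands. Replacing the worldwide total by that of the 24 countries moves 1,534 only to 1,525. Dropping the finite-population correction leaves 19 of 24 countries within ±10.4.

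It is also fair that the Discussion admits selection bias and wide country intervals. It does so without withdrawing or qualifying either figure.

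Two stronger readings are tempting and are not supported. A reader might infer that the published intervals will be too narrow. The Sample size section concerns planning only, nothing says that reported intervals will use the planning formula, and variance estimation may be set out in a document not shown. A reader might also inflate the global margin by treating countries as a random draw with their own ICC. The documents do not describe the 24 countries as such a draw, and a between-country variance term would conflict with treating them as fixed strata.

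**Conclusion.** The concern holds as a fault in the stated precision. Both margins are nominal simple-random-sample values presented as what the study would provide, and the design described in the same article does not provide them. The size depends on the estimand. If the global figure represents women in the 24 countries by prevalence, the stated margin is less than half the attainable one (2.5 against 5.4 at 2,160 or 6.4 at 1,534). That result needs only Table 2 and p = 0.5. If the figure is an unweighted or equal-weight average, the shortfall comes from clustering: none to about 1 point at 2,160, and 0.2 to 1.3 points at 1,534, over the assumed ICC range. For countries it is up to 1.7 points before clustering, and about 1 to 7 points at n = 90 after it.

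The ICCs are assumptions. All these margins remain nominal, because no design effect accounts for bias from convenience selection. The calculation formula itself is applied correctly; it does not fit the design.

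**What to change.** In the Sample size section:
- Label ±2.5% and ±10% as nominal simple-random-sample figures, or withdraw them.
- Name the global estimand, either an equal-weight or unweighted average over the 24 countries or a Table 2 prevalence-weighted average, and give its margin before site clustering: about ±2.1 points at 2,160 (±2.5 at 1,534) for the former, about ±5.4 (±6.4) for the latter.
- Add the effect of clustering over a stated ICC range. For the unweighted estimate and ICC 0.01 to 0.10 this is ±2.3 to 3.5 at 2,160 and ±2.7 to 3.8 at 1,534.
- Restate the country margin without the finite-population correction as about ±10.0 to 11.7 points before clustering, and about ±11 to 17 at n = 90 with about 19 women per site.
- Specify country strata with site-clustered variance where a country has several sites. Note that between-site variance cannot be estimated in a country with one site.
- State that no margin covers selection bias.

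Recruitment is unchanged. The cost is rewording and standard survey-variance code, and the stated precision becomes less favourable.

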### Data analysis

In our analysis, we seek to examine variation in key metrics (such as stage of ovarian cancer, time to diagnosis and levels of awareness) by country, region and by the socio-economic country group. In addition, we will explore associations between patient and country characteristics and key outcome measures. Table 3 gives some examples of the outcome variables and expected areas for further analysis.

**Table 3 pone.0298154.t003:** Outcome variables and expected further analysis.

Outcome variables		
• Access to chemotherapy • Access to optimal cytoreductive surgery • Access to genetic testing • Level of ovarian cancer knowledge • Time to seek help • Time from seeking help to obtaining a diagnosis • Time from diagnosis to treatment • Information needs •Impact on family finances •Priorities for action		

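### The Sample size text and Table 2 disagree by a net two countries on income group, a planned analysis factor

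*Protocol article*

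**What the plan says.** The Sample size section gives the income split in words: "24 countries (3 low, 11 lower-middle and 10 upper-middle income countries". The same sentence gives the total if every country meets its minimum ("collect their minimum data, the sample size would be 2,160 (Table 2").

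Table 2, captioned "Expected sample sizes by country and income level", attaches an income label to each of the 24 countries. Its column header cites the World Bank status of June 2021.

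Study infrastructure names a single source: "Classification of country income level was determined using the World Bank open data, accessed in June 2021".

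The Data analysis section plans to examine variation in key metrics "by country, region and by the socio-economic country group". It also plans descriptive and inferential statistics by economic grouping.

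**The concern.** A country has one income status in one dated source. The sentence and the table it refers to claim the same source and date, yet they give different numbers of lower-middle and upper-middle countries. They cannot both be right.

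This is more than a slip in background description, because income group is one of the axes on which results will be compared. An analyst or outside reader who builds the grouping variable from Table 2 gets a 13/8 split, while the narrative reports 11/10. If the table is the wrong side, whole countries change group. That error is systematic, and recruiting more women does not dilute it. The low-income group has only three countries, so lower-middle against upper-middle is the largest income comparison available, and those are the two groups in doubt.

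**Working it through.** **Inputs.** Income labels and minimum sample sizes come from Table 2. The stated split and totals come from the Sample size text. The global five-year prevalence comes from the Introduction ("more than 823,000 women living within five years of their diagnosis").

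**Step 1: count the labels and sum the minima.**

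| Label in Table 2 | Countries (minimum size) | Count | Text says | Sum of minima |
|---|---|---|---|---|
| Low | Malawi 79, Mozambique 70, Uganda 89 | 3 | 3 | 238 |
| Lower-middle | Ghana 92, Kenya 92, Nigeria 95, South Africa 94, Zambia 78, Egypt 95, Morocco 93, Vietnam 95, Kazakhstan 93, Uzbekistan 92, Bangladesh 95, India 96, Nepal 89 | 13 | 11 | 1,199 |
| Upper-middle | Malaysia 94, Argentina 95, Brazil 96, Colombia 95, Guatemala 83, Jamaica 72, Mexico 95, Peru 93 | 8 | 10 | 723 |
| All | | 24 | 24 | 2,160 |

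The stated total reproduces: 238 + 1,199 + 723 = 2,160. The number of countries and the low-income count also agree. The lower-middle count is two above the text and the upper-middle count two below it. The income entry on the Total row was not counted.

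**Step 2: size of the discrepancy if the text is right.** Suppose exactly two rows labelled lower-middle belong in upper-middle.

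- Smallest pair: Zambia 78 + Nepal 89 = 167 women. Lower-middle becomes 1,199 − 167 = 1,032, and upper-middle 723 + 167 = 890.
- Largest pair: India 96 + one of the countries at 95 = 191 women. Lower-middle becomes 1,199 − 191 = 1,008, and upper-middle 723 + 191 = 914.
- Share of the labelled lower-middle group that would not belong there: 167/1,199 = 13.9% to 191/1,199 = 15.9%.
- Share of the true upper-middle group that would be missing from it: 167/890 = 18.8% to 191/914 = 20.9%.

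**Step 3: does the discrepancy touch the sample sizes?** The minima are set by prevalence and precision ("producing results at the 95% confidence level (+/- 10"), not by income group, so 2,160 stands whichever split is right. The global target is stated as "at least 1534 women, which would provide results at a 95% confidence level, +/- 2.5%, based on global five-year prevalence". With n0 = z² × 0.25/e² and n = n0/(1 + (n0 − 1)/N), taking z = 1.96, e = 0.025 and N = 823,000, n0 is about 1,536.6 and n = 1,533.7. This rounds up to 1,534. Income group does not enter the formula.

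**The case against.** A reader might infer that two countries will be analysed in the wrong economic group. The documents do not support that, for three reasons.

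- The sentence may be the wrong side. If so, a count in parentheses is wrong and no country is misplaced.
- Nothing says that Table 2 is the lookup for the analysis. The named source is the World Bank data, and the table is captioned as a sample size table.
- Two is a net difference. The number of wrong labels could be none, or more than two if there are offsetting errors. Fig 1 also shows countries by income level, but it is not visible here and cannot settle the matter.

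A reader might also divide the 167 to 191 women by the 723 labelled upper-middle and report 23-26%. That denominator is itself wrong in the scenario assumed, so the shares under working are the ones to use.

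The plan names no specific lower-middle versus upper-middle contrast. The example regressions in Table 3 use patient and site variables, not country income group. The exposure is therefore in the planned summaries and tests by economic grouping. The income entry on the Total row of Table 2 may be an artefact of reading the table and is not counted as an error.

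All of this narrows the consequence but does not remove the contradiction. Table 2 cannot simply be presumed correct either. Its preferred-size column sums to 7,554 against a stated 6,815. Morocco's listed prevalence of 395 gives about 77 under the formula above at ±10% (96.04/(1 + 95.04/395) = 77.4), against a listed minimum of 93. On the other hand, all 24 rows carry a label, and the minimum and prevalence columns sum to their stated totals (2,160 and 198,713). Broken extraction of the rows is therefore an unlikely explanation.

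**Conclusion.** The point holds as an internal contradiction that is wrong as written: 3/11/10 in the text against 3/13/8 in Table 2, on a factor the analysis will use.

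The consequence is conditional. At least two countries could be placed in the wrong group only if the text is right and the grouping is taken from the Table 2 labels. The sizes in step 2 assume minimum recruitment and exactly two rows moving in one direction; they would change with larger recruitment or offsetting errors. If the table is right, the only correction is to the counts in the sentence. Which side is wrong, and which countries are affected, cannot be decided from the document.

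**What to change.** Check the income label of all 24 countries against the June 2021 World Bank source that the article cites. Correct Table 2 or the counts in the Sample size text, whichever is wrong, and confirm that Fig 1 agrees. Use the reconciled classification as the income-group variable in the analysis. The cost is a 24-row check and a correction to one sentence or to some table labels. Design, recruitment targets and data collection do not change.
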